### Objectives

The primary objective of this randomized experiment is to investigate whether adaptive individualized feedback is superior to standardized feedback in smartphone-based emergency neonatal care training. We hypothesize that health care providers randomized to receive adaptive feedback will have a significant improvement in learning gains as compared to those randomized to receive standardized feedback.

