**Methods:**

The study is aimed at health care workers (physicians, nurses, and clinical officers) who provide bedside neonatal care in low-income settings. We will use data captured through an Android smartphone-based serious-game app that will be downloaded to personal phones belonging to the study participants. The intervention will be adaptive feedback provided within the app. The data captured will include the level of feedback provided to participants as they learn to use the mobile app, and performance data from attempts made during the assessment questions on interactive tasks participants perform as they progress through the app on emergency neonatal care delivery. The primary endpoint will be the first two complete rounds of learning within the app, from which the individuals’ “learning gains” and Morris G intervention effect size will be computed. To minimize bias, participants will be assigned to an experimental or a control group by a within-app random generator, and this process will be concealed to both the study participants and the investigators until the primary endpoint is reached.

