### Outcomes

The primary endpoint for both arms of the experiment will be the presence of two complete rounds of learning sessions using LIFE, the former is the pretest round and the latter is the posttest round. Both scores will be converted into percentages. From the pre-post scores, the study’s main outcome—the learning effect size (*d*), [35]—will be calculated as follows:

where the pooled SD is defined as:

The bias adjustment is provided by the formula:

where *n*_*T*
_ is the sample size of the treatment group, *M*_*pre,T*
_ is the pretest mean for the treatment group, *M*_*post,T*
_ is the posttest mean for the treatment group, *SD*_*pre,T*
_ is the SD of means for pretest in the treatment group, *SD*_*post,T*
_ is the SD of means for posttest in the treatment group, *n*_*C*
_ is the sample size of the control group, *M*_*pre,C*
_ is the pretest mean for the control group, *M*_*post,C*
_ is the posttest mean for the control group, *SD*_*pre,C*
_ is the SD of means for pretest in the control group, and *SD*_*post,C*
_ is the SD of means for posttest in the control group.

The effect size from equation from (1) is referred to as *Morris G* [35] and represents the mean difference between the study groups. Because of randomization, this calculation allows to control for pre-existing differences among learners (eg, intelligence quotient level), to estimate treatment effectiveness even when the treatment and control groups are not equivalent, and to consider the variances of both pretest and posttest scores. This contrasts with other forms of effect-size calculation such as Hedges G and Becker D, which only use pretest or pooled variances [35]. In this model, the pretest and posttest variances are assumed to be homogeneous.

Secondary outcomes that will be assessed are time difference between each round of learning sessions, the number of times a learner has encountered a learning task up to the current opportunity (ie, cumulative attempts on learning task per learner), the time spent on each learning task, and the level of feedback provided. These calculations will be performed in Python, version 3.6.8 (Python Software Foundation, Wilmington, DE).

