### Statistical Methods and Planned Analysis

For the primary endpoint, we will use the Morris G effect size to analyze the differences among group means in the study population. This will be assessed after the performance from the second round of training through the mobile app has been recorded. Secondary analysis will be conducted using regression analysis, with learning gains as the dependent variable and the aforementioned secondary outcomes as the independent variables, to evaluate their effect on learning gains. Learning gains, defined as the amount the health care providers learned divided by the amount they could have learned [40], will be calculated with the formula given in Equation 8 in Multimedia Appendix 1.

Due to the definition of the primary learning outcome used in this study, the outcome cannot be computed for study participants whose dropout is characterized by the lack of at least two complete learning sessions. Without a postbaseline assessment, “intention-to-treat” analysis cannot be performed for dropout cases unless we impute outcomes, which tends to produce biased estimates [41]. This study will not be able to conduct an intention-to-treat analysis. However, dropout numbers will be reported in relation to those who reached the study’s primary endpoint, and their implications will be discussed with regard to self-regulated self-directed learning [37-39].

Qualitative interviews will be conducted in parallel with the experiment for participants who have reached the primary endpoint and those who drop out. These interviews will be used to explore how self-regulation in learning affected the use of the smartphone-based learning platform and to provide context for interpreting the observed learning outcomes from this study apart from offering evidence for tool validation.

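### The hypothesis is stated on learning gains, but learning gains as the protocol defines them are not compared between the randomised arms in any stated analysis

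*Protocol article*

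**What the plan says.** - **Objectives.** The aim is superiority of adaptive over standardised feedback. The hypothesis is that the adaptive group "will have a significant improvement in learning gains as compared to those randomized to receive standardized feedback". The term learning gains is not defined there.
- **Abstract, Methods.** The primary endpoint is two complete rounds of learning, "from which the individuals’ “learning gains” and Morris G intervention effect size will be computed". Two separate quantities are thus named.
- **Outcomes.** The pretest and posttest scores are put on one scale: "Both scores will be converted into percentages". Then: "From the pre-post scores, the study’s main outcome—the learning effect size" (Morris G), which "represents the mean difference between the study groups".
- **Statistical Methods and Planned Analysis.** Morris G is used for the primary endpoint. Learning gains appear in the secondary analysis, "defined as the amount the health care providers learned divided by the amount they could have learned", with the formula in Equation 8 of Multimedia Appendix 1 (not shown). They are the dependent variable of a regression whose independent variables are the secondary outcomes.
- **Outcomes, secondary list.** These are the time between rounds, cumulative attempts on a task, time spent on each task, and level of feedback provided.

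**The concern.** The term in the hypothesis and the metric in the primary analysis differ. A reader who applies the protocol's own definition expects a between-arm comparison of normalised gain. A reader who follows Outcomes expects a standardised difference in percentage scores. The analysis plan delivers the second and has no by-arm version of the first.

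The secondary regression does not fill the gap. Its regressors are all measured after allocation, and arm is not among them. Level of feedback is not a stand-in for arm, because the level a learner receives depends on that learner's own errors. The regression therefore describes how process variables go with learning gains; it does not estimate the effect of adaptive feedback on them.

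At stake is whether the reported result answers the hypothesis as worded, and whether the secondary analysis says anything about the randomised question.

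**Working it through.** **1. The passages side by side**

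| Section | Quantity | Role | Compared by arm? |
|---|---|---|---|
| Objectives | Learning gains (undefined there) | Hypothesis | Yes, in the wording |
| Abstract, Methods | Learning gains and Morris G | Both to be computed | Not stated for learning gains |
| Outcomes | Morris G on percentage scores | Main outcome | Yes |
| Statistical Methods | Morris G | Primary endpoint | Yes |
| Statistical Methods | Normalised gain | Dependent variable, secondary regression | No arm term listed |

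The only other modelling that names the study groups is the logistic regression under Sample Size Calculation. It concerns bias from attrition and does not compare learning gains.

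**2. The two metrics**

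With scores in percent, the verbal definition of learning gain is

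g = (post − pre) / (100 − pre).

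Morris G contrasts the arms' mean changes on the percentage scale:

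[(mean post − mean pre) adaptive − (mean post − mean pre) control] / pooled SD.

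The first weights a point gained by the learner's remaining room; the second does not. For example, 15 points gained from a pretest of 60 gives g = 15/40 = 0.375.

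**3. Can they diverge?**

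The inputs are assumptions, not protocol figures: pretest mean 60, SD 15, limited to 5–95; posttest limited to 0–100; noise SD 8 points (6 in the proportional case); 200,000 simulated learners per arm. Control gains 15 points, or 38% of the available room in the proportional case. The Morris-type effect divides by the root of the average of the four pre and post variances. The normalised-gain difference is divided by its own pooled SD.

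| Scenario, adaptive arm | Morris-type effect | Standardised difference in g |
|---|---|---|
| +18 points for all | 0.18 | 0.27 |
| 45% of available room | 0.22 | 0.32 |
| +20 if pretest below 60, otherwise +12 | 0.08 | 0.00 |
| +12 if pretest below 60, otherwise +18 | −0.02 | 0.05 |

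The measures mostly move together. They part when the benefit depends on the pretest, and in the last row they differ in sign, though both values are close to zero. For scale, the protocol's Results section calls about 0.2 a small effect.

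**4. The definition at the ceiling**

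At a pretest of 100% the denominator is 100 − 100 = 0, so g as worded does not exist. Just below the ceiling it is unstable: with 20 tasks, a pretest of 95% leaves a denominator of 5, and a fall of 40 points gives −40/5 = −8.

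How often a perfect pretest occurs depends on assumed inputs (logit-normal ability, SD 1):

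| Number of tasks | Pretest centre | Perfect pretest |
|---|---|---|
| 20 | 30–50% | about 0.1–0.6% |
| 20 | 60–80% | about 1.5–8% |
| 40 | 60–80% | about 0.3–2.4% |

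The protocol gives neither the number of tasks nor an expected pretest score.

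**The case against.** The strongest reply is that the hypothesis is tested. Objectives leaves learning gains undefined, and the abstract's Objective speaks simply of knowledge gain. Read as pre-to-post improvement, the hypothesis is what Morris G addresses, since it contrasts the arms on exactly that. This stands. A reader might infer that the trial's hypothesis goes untested; the documents do not support that.

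A reader might also infer two rival primary metrics, leaving room to choose the favourable one. That does not hold either. Outcomes names Morris G as the main outcome, and Statistical Methods puts learning gains under secondary analysis. The abstract says only that both will be computed. The division also has a rationale: a regression needs an individual-level outcome, which a group-level effect size cannot supply.

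Third, the word significant in the hypothesis has no test or confidence interval named beside Morris G. A condensed article commonly leaves that to a fuller plan, and the sample size section does state a two-sided 5% level. It is not counted here.

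Fourth, the ceiling problem rests on a verbal definition. Equation 8 is not shown and may deal with a 100% pretest. Raw percentages have a ceiling too, so Morris G is not free of the issue, although it stays defined. Both points stand, which is why the ceiling is a side remark.

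None of this supplies an arm term for the learning-gains regression, or makes the hypothesis and the primary metric use the same term.

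**Conclusion.** The mismatch is real and limited. The hypothesis uses a term that the protocol defines only as a normalised gain; the primary analysis uses Morris G on percentage scores; and no stated analysis compares the normalised gain between arms. Morris G remains the primary metric and answers the hypothesis in its ordinary sense.

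The textual finding needs no assumptions. Its practical size does. In the four illustrative scenarios the two metrics differed by 0.07 to 0.10 standardised units (0.27 − 0.18 = 0.09; 0.32 − 0.22 = 0.10; 0.08 − 0.00 = 0.08; 0.05 + 0.02 = 0.07). The frequency of an undefined gain ran from about 0.1% to 8% across pretest centres of 30–80% with 20 tasks, and was lower with more tasks. Whether Equation 8 already handles that case is unknown.

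**What to change.** 1. Reword the hypothesis in Objectives, and the primary-endpoint sentence in the abstract, to the between-arm pre-post difference in percentage score expressed as Morris G. State that this is the single primary metric.
2. Keep learning gains secondary, but compare them by randomised arm, in a model without the four post-randomisation variables. The existing regression on those variables can remain, labelled as descriptive of process.
3. If learning gains are kept, state how a 100% pretest is handled. Alternatively, replace them with the posttest score adjusted for pretest, which uses data already collected and is defined at every pretest value.

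The cost is a few sentences and one extra secondary model, with no new data. The Results section says the full analysis is still to come, so the change can be recorded before it is run.

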## Methods

### Study Design

The study (trial registration: Pan African Clinical Trials Registry PACTR201901783811130) will have a parallel-group double-blinded randomized experiment design with an allocation ratio of 1:1. The participants will be randomized to the intervention or control group when they launch the android-based training app for the first time on their individual smartphone devices.

### Eligibility Criteria

Health care workers who are in nursing, clinical, or medical professional cadres that offer bedside patient care are included. Additionally, health care workers in practice and those in training are eligible for inclusion into the experiment. Health care workers who have retired from clinical practice and participants who are not health care workers will be excluded from the study.

### Study Setting and Recruitment

This study does not have a specific physical study site; it focuses on low-income countries that stand to benefit from ETAT+ training. Distribution of the intervention is through the Google Play Store, with initial efforts directed toward physical recruitment in Kenya. Recruitment of study participants will be through three main avenues: (1) remotely, by raising awareness of the Android Google app on social media platforms and online health networks forums every couple of weeks during the study duration to promote voluntary, self-enrolment for use of the training tool; (2) use of snowballing sampling by ETAT+ trainers, previous study participants, and lecturers in medical sciences at local Kenyan universities to suggest that (and encourage) other health workers to self-recruit into the study; and (3) use of a study sample from the purposive selection strategy that will be actively convened once every month, with a unique set of participants to ensure the participant recruitment targets are diverse and met. Snowballing sampling is a type of convenience sampling where a group of people (in our case, already recruited participants) recommend potential participants for the study [28]. The cycle of recommendation of participants for inclusion into the study continues during the study duration. This also serves as an indicator of LIFE intervention adoption. The first avenue includes platforms that are focused on health capacity building in the global south in line with LIFE’s focus on low-income contexts. Avenues 2 and 3 will take place at the following sites: Kenyatta National Hospital - Neonatal Nurse Training Unit; College of Health Sciences, University of Nairobi; Kenya Medical Training College (Nairobi); and Gertrude’s Garden Children’s Hospital Nurse Training School (Nairobi).

### Intervention

The intervention in this study involves adaptive, personalized, and immediate feedback that is provided while learning through a smartphone-based serious gaming Android app. The content to be learned is based on ETAT+ guidelines, a course that is already offered in nine low-income countries [7,8,10]. The intervention will be available on the Google Play Store where it will be publicly accessible, downloadable, and installable to any compatible android-based mobile device. All study participants will receive a link to the mobile app hosted on the Android Play Store. The LIFE app was designed for Android’s Target SDK 19 as the minimum version of Android supported as of February 2019 (which targets 100% of Android devices) [29]. Given that the intervention has undergone alpha and beta testing on health care providers’ smartphones since October 2017 in Kenya, we are confident of the stability of the app.

The personalized immediate feedback to be given to the experimental group participants is designed to arouse meaningful immersive learning experiences from continuous interaction between the learners and the smartphone-based training [30,31]. This adaptive feedback will be provided to experiment group participants after each incorrect attempt at a learning task with three cascading detail levels based on predicted probability that the learner’s next attempt is going to be correct. The wording of the feedback provided is dependent on the number of incorrect choices the learner had selected and the actual incorrect choices themselves. The control group study participants will receive standardized nonpersonalized immediate feedback after each incorrect attempt at a learning task, with the feedback on the first incorrect attempt asking the learner to retry and the feedback on the second attempt providing a detailed explanation of the correct choices to select.

The LIFE app is a measurement tool; at the end of successful completion of a learning session, the platform provides performance scores based on whether each learner’s response to the learning task was correct on the first attempt.

This methodology mimics a common approach in experimental design known as A/B testing, which is used to optimize concepts such as feedback or user interface on digital platforms [32,33]. In particular, the experiment described here emulates A/B tests’ commonly used Hypothesis Experiment Data‐Driven Development model, whose description and use are detailed elsewhere [34]. Such an experimentation approach can be used for digital health interventions where there is need for data-driven decision making on inclusion of features and the data are trustworthy, but assessment of the added value of features on the digital platform is difficult [33].

### Outcomes

The primary endpoint for both arms of the experiment will be the presence of two complete rounds of learning sessions using LIFE, the former is the pretest round and the latter is the posttest round. Both scores will be converted into percentages. From the pre-post scores, the study’s main outcome—the learning effect size (*d*), [35]—will be calculated as follows:

where the pooled SD is defined as:

The bias adjustment is provided by the formula:

where *n*_*T*
_ is the sample size of the treatment group, *M*_*pre,T*
_ is the pretest mean for the treatment group, *M*_*post,T*
_ is the posttest mean for the treatment group, *SD*_*pre,T*
_ is the SD of means for pretest in the treatment group, *SD*_*post,T*
_ is the SD of means for posttest in the treatment group, *n*_*C*
_ is the sample size of the control group, *M*_*pre,C*
_ is the pretest mean for the control group, *M*_*post,C*
_ is the posttest mean for the control group, *SD*_*pre,C*
_ is the SD of means for pretest in the control group, and *SD*_*post,C*
_ is the SD of means for posttest in the control group.

The effect size from equation from (1) is referred to as *Morris G* [35] and represents the mean difference between the study groups. Because of randomization, this calculation allows to control for pre-existing differences among learners (eg, intelligence quotient level), to estimate treatment effectiveness even when the treatment and control groups are not equivalent, and to consider the variances of both pretest and posttest scores. This contrasts with other forms of effect-size calculation such as Hedges G and Becker D, which only use pretest or pooled variances [35]. In this model, the pretest and posttest variances are assumed to be homogeneous.

Secondary outcomes that will be assessed are time difference between each round of learning sessions, the number of times a learner has encountered a learning task up to the current opportunity (ie, cumulative attempts on learning task per learner), the time spent on each learning task, and the level of feedback provided. These calculations will be performed in Python, version 3.6.8 (Python Software Foundation, Wilmington, DE).

### Participant Timeline

Enrolment of study participants began on February 1, 2019, and will continue up to July 31, 2019. Because the rollout of LIFE’s intervention in this study is based on the principles and outcomes of an implementation study [36] and informed by self-regulated self-directed learning [37-39], it seeks to understand and work within real-world conditions, rather than trying to control for adoption, acceptability, coverage, and sustainability conditions or remove their influence on the study outcome [36]. Subsequently, to optimally maintain fidelity to LIFE’s planned scale-up, no training sessions are planned for the study participants. Although LIFE is designed for low-income contexts, we set no limit by geographical coverage for self-directed health care providers who might be interested in undertaking this training. However, for primary outcome analysis, participants from high-income countries will be omitted. Participants without any geographic location data (due to refusal to grant the LIFE app the required Android permissions) will be assumed to be from developing countries, given that our recruitment efforts are directed toward professional groups in these countries.

### Sample Size Calculation

Similar interventions in other subject domains have been found to have an mean effect size of 0.22 (95% CI 0.16-0.27) from a meta-analytic fixed-effects model [24]. To detect an effect size of 0.22 with a two-sided 5% significance level and a power of 80%, a sample size of 83 participants per group, who reach the primary endpoint of the study, is necessary. A sample size calculation for a one-way ANOVA, together with one-sample and paired-sample *t* test analysis using the same effect, power, and significance parameters produce the same required sample size. We anticipate recruiting this number of participants (N=166) in 6 months. The sample size calculation formula is given in the Multimedia Appendix 1.

Based on the alpha and beta tests of the LIFE version, we are assuming a 50% dropout rate of study participants, with drop-out defined as the incomplete or single use of the LIFE smartphone app. We plan to recruit at least 332 participants to account for this dropout rate. To encourage repeated usage of LIFE, participants will receive up to three email reminders from the time they are enrolled into the study, spread over 3 weeks. Demographic data will be collected in the app during its initial use by study participants at the end of the first learning session. Thus, for learners who drop out before completing the first session, or chose not to fill in those data, no demographic data will be available. Logistic regression analyses will be performed on these data to evaluate whether there is a systematic bias caused by attrition of study participants that affects the interaction between the study groups and performance, exposure to previous ETAT+ training, clinical cadre, age of participant, and level of experience. In an effort to ensure participant recruitment is at par with the required study sample size, a monthly target of 30 participants, evaluated at the end of each month, has been set for this study.

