## Results

This project was funded in November 2016. Data were collected from February 2019 up to July 2019. As of July 2019, we enrolled 541 participants, of whom 238 reached the primary endpoint, with a further 19 qualitative interviews conducted to support evaluation (New-Born Unit in-charge nurses, n=4; Paediatric Intensive Care Unit nurses, n=5, final-year medical students already doing clinical rotations, n=4; and student clinical officers and nurses already doing clinical rotations, n=6). Full analysis will be conducted once the number of required participants is met, and the results are expected to be published by Spring of 2020.

Based on the education literature [24,44,45], an effect size of approximately 0.2, 0.5, and 0.8 will be considered small, moderate, and large, respectively. These thresholds represent the magnitude of effect and reflect our assumption that a statistically significant result is not necessarily important or meaningful; for example, for an effect size of 0.2, the difference between the study groups is trivial even if it is statistically significant [44,46].

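### The stated 83 completers per group do not give 80% power for a between-arm effect of 0.22; an unadjusted comparison needs about 326 per group, and 83 gives about 29% power

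*Protocol article*

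**What the plan says.** All of the sizing is in the protocol article, Sample Size Calculation.

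- The target comes from a meta-analysis in other subject domains: "mean effect size of 0.22 (95% CI 0.16-0.27) from a meta-analytic fixed-effects model".
- The required size in each arm, counting completers only, follows: "To detect an effect size of 0.22 with a two-sided 5% significance level and a power of 80%, a sample size of 83 participants".
- A one-way ANOVA and one-sample and paired t tests are then offered as confirmation: "test analysis using the same effect, power, and significance parameters produce the same required sample size". A two-sample t test is not named.
- The total is carried forward: "We anticipate recruiting this number of participants (N=166) in 6 months", and, at 50% dropout, "We plan to recruit at least 332 participants to account for this dropout rate".

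The Study Design section describes two parallel arms allocated 1:1. Outcomes, and Statistical Methods and Planned Analysis, make Morris G the main outcome. It is computed from pretest and posttest scores and is described as a mean difference between the study groups. The Results section reads effect sizes against benchmarks of 0.2, 0.5 and 0.8, and adds that "for an effect size of 0.2, the difference between the study groups is trivial even if it is statistically significant".

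**The concern.** The outcome label (d), its description as a between-group mean difference, and the 0.2/0.5/0.8 benchmarks all place 0.22 on the standardized-mean-difference scale, as a contrast between two independent arms. On that scale 83 per group looks about four times too small. The sentence on agreeing calculations points to the reason. One-sample and paired tests concern a single group, and a total from such a test is not a per-arm number for a two-arm contrast.

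This is the article's only power statement for its primary objective, which is framed as a significant improvement with adaptive feedback. If the stated power is wrong, so is the claim that 166 completers and 332 enrolments are what an effect of 0.22 requires. Readers would also have the wrong basis for judging how much a non-significant result says.

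**Working it through.** **Inputs.** Effect 0.22 (95% CI 0.16 to 0.27), two-sided 5%, power 80%, 83 completers per group, 166 in total, dropout 50% (Sample Size Calculation); two arms, 1:1 (Study Design); 541 enrolled and 238 completers (Results). Results below use the noncentral t or F distribution.

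**1. Reproducing 83.**
- One-sample or paired t test, standardized effect 0.22: n = 164.1, so 165 in total. Half of 165 is 82.5, which rounds up to 83.
- One-way ANOVA, two groups, Cohen's f = 0.22: total 164.1, or 82.05 per group, which rounds up to 83. Power at a total of 166 is 80.5%.

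The calculations named in the article therefore do agree, but on a total of about 165. For two equal groups d = 2f, so f = 0.22 is d = 0.44.

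**2. The two-arm comparison at d = 0.22.**
- Normal approximation: n per group = 2(1.960 + 0.842)² / 0.22² = 2 × 7.849 / 0.0484 = 324.3, so 325.
- t test: 325.3, so 326 per group, or 652 completers. At 50% dropout, 652 / 0.5 = 1,304 enrolled.
- ANOVA with the matching f = 0.22 / 2 = 0.11: total 650.6, which is the same answer.
- A one-sided test (256 per group) does not give 83 either.

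**3. What 83 per group delivers, unadjusted.**

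| True d | Power at 83 per group |
|---|---|
| 0.16 (lower CI limit) | 18% |
| 0.22 (target) | 29% |
| 0.27 (upper CI limit) | 41% |
| 0.44 | 80% |

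**4. Allowing for pre-post change.** G contrasts pre-post changes, and the article assumes equal pretest and posttest variances. If 0.22 is in raw-score SD units, a change score has SD sqrt(2(1 − rho)) in those units, where rho is the pre-post correlation. The effective standardized effect is then 0.22 / sqrt(2(1 − rho)). The article gives no rho, so the values below are an assumed range.

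| rho | Effective effect | Power, 83 per group | Power, 119 per group |
|---|---|---|---|
| 0.3 | 0.186 | 22% | 30% |
| 0.5 | 0.220 | 29% | 39% |
| 0.7 | 0.284 | 44% | 59% |
| 0.8 | 0.348 | 61% | 76% |

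The 119 column is 238 / 2. It assumes an even split and no exclusions.

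The effect detectable with 80% power at 83 per group is 0.437. Setting 0.22 / sqrt(2(1 − rho)) = 0.437 gives rho = 1 − (0.22 / 0.437)² / 2 = 0.87.

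**5. Dropout step.** 166 / (1 − 0.5) = 332. This step is correct; only its input is wrong.

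**The case against.** The strongest defence is that Morris G is built on pre-post scores, so the unadjusted two-sample formula need not apply. With a high enough pre-post correlation, 83 per group would be sufficient. In principle that is right, and it means 29% should not be quoted without its condition. It does not rescue the stated figure. The article states no correlation, about 0.87 would be needed, and the calculations it names are said to use the same effect with no correlation adjustment.

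A second defence is that the formula is in Multimedia Appendix 1, which is not shown. This limits what can be said about the cause: the f-for-d or halved-total explanation fits the numbers but remains an inference. The shortfall itself does not depend on it.

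Third, recruitment went past plan, to 238 completers. That helps, but an unadjusted comparison with 119 per arm still has only 39% power at 0.22. The real numbers may be less favourable, because participants from high-income countries are omitted from the primary analysis and allocation is a simple coin toss.

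Three stronger readings are tempting, and the article does not support them.
- A reader might infer that an observed 0.22 could never be significant at this size. The unadjusted threshold at 83 per group is 0.307, but for a change score it is 0.307 × sqrt(2(1 − rho)). This falls below 0.22 once rho exceeds about 0.74, and is 0.19 at rho = 0.8.
- A reader might set the monthly target of 30 (180 over six months) against 332 enrolments. The text does not say whether that target counts enrolments or completers, and 180 covers 166.
- A reader might say a null result would be taken as evidence against adaptive feedback. The planned analysis is an effect size, and the Results section stresses magnitude over significance, so that misreading is possible but is not written into the plan.

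**Conclusion.** The stated sample size is wrong as written. For a standardized difference of 0.22 between two arms, an unadjusted comparison needs about 326 completers per group, roughly four times the stated 83. With 83 per group the power is about 29%, and no value inside the article's own interval of 0.16 to 0.27 gets above 41%. The size has 80% power only for about 0.44.

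The 29% holds for an unadjusted comparison, or for a change-score comparison at rho = 0.5. Over rho from 0.3 to 0.8 the change-score figure is 22% to 61%, all below 80%. The conclusion would fail only if a correlation of about 0.87 or more had been assumed, and nothing in the article says so.

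A smaller inconsistency goes with it: the article sizes the trial for 0.22 while describing a difference of 0.2 as trivial.

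**What to change.** In Sample Size Calculation:

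1. Replace the power statement with one of this kind: 83 completers per group give 80% power for a standardized between-arm difference of about 0.44 and about 29% for 0.22 (unadjusted, or pre-post correlation 0.5); for correlations of 0.3 to 0.8 the power for 0.22 is 22% to 61%. If a particular correlation was assumed, state it and its source.
2. Delete the sentence saying that ANOVA, one-sample and paired calculations give the same size.
3. Keep 166 and 332 as the planned numbers, but stop describing them as what an effect of 0.22 requires.
4. Give 0.44 as the detectable effect, not as a new target. It lies well outside the cited interval of 0.16 to 0.27, and adopting it after 541 enrolments would fit the target to the sample.

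In Statistical Methods and Planned Analysis, make G with its 95% CI the main result and state that a non-significant result does not exclude 0.22. In Results, acknowledge that the sizing effect is close to the value called trivial there.

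The cost is wording only. No further participants are needed, and the full analysis was still to come when the article was written. The price is a less favourable power statement.
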